#### Interim analyses {21b}

No interim analysis will be performed because of the short duration of the trial and a minimal intervention risk.

#### Methods for additional analyses (e.g., subgroup analyses) {20b}

See Statistical Methods for primary and secondary outcomes.

#### Methods in analysis to handle protocol non-adherence and any statistical methods to handle missing data {20c}

The intent-to-treat method will be used in conjunction with a LME model, which is recommended for longitudinal data with missingness.

#### Plans to give access to the full protocol, participant-level data and statistical code {31c}

Not applicable, We have no plans in relation to this.

### Oversight and monitoring

#### Composition of the coordinating center and trial steering committee {5d}

No data monitoring committee (DMC) will be established for this trial because the trial is short and limited to a single center.

#### Composition of the data monitoring committee, its role and reporting structure {21a}

No DMC will be established for this trial.

#### Adverse event reporting and harms {22}

Patients in the intervention group will be assessed for adverse events at weeks 2 and 6. All cases of serious adverse events will be reported to the Danish Scientific Ethics Committee.

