#### Intervention description {11a}

The intervention group receives transdiagnostic sleep treatment consisting of six individual sessions lasting 60 min each in the course of 6 weeks. The sessions are conducted by a team of nurses, a physiotherapist, an occupational therapist, and a psychologist. These professionals have undergone a minimum of a two-day intensive theoretic sleep course to enhance their knowledge and skills in the field of sleep. Subsequently, they have received peer-to-peer training. Training and supervision are provided by the first and second authors of this paper.

The sessions have the following contents:Assessment and introduction to the sleep diary. The items from the sleep diary are similar to those of the consensus sleep diary [35]Sleep restriction, sleep compression, stimulus-control, or phase advance. Setting goals [10]Education about normal sleep, sleep problems, and circadian rhythmCognitive techniques (e.g., behavioral experiments) [10]Introduction to relaxation training (e.g., progressive muscle relaxation) [36]Follow-up on goals and plan for preventing sleep problem relapse

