### Criteria for discontinuing or modifying allocated interventions {11b}

The allocated intervention will be discontinued on the patient’s request, and patients may withdraw from the study for any reason. The investigators have the discretion to withdraw patients from the study if their mental disorder is deteriorating, e.g., if they experience a manic episode, are at an acutely increased suicide risk, or if they are hospitalized for any reason.

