#### Plans to promote participant retention and complete follow-up {18b}

Patients who deviate from intervention protocols due to, e.g., illness, are asked to complete the questionnaires as soon as possible. We offer to do this with the patients by phone, at a home visit or virtually based on the patient’s preference. We also allow a flexibility of + / − of 7 days from the planned follow-up visits.

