## Discussion

The strengths of the study are the use of both subjective and objective data. Furthermore, we investigate patients´ daytime functioning, which is important because sleep problems influence quality of life around the clock. Results from this trial will contribute to knowledge on the effect of the intervention and pave the way for implementing the most effective sleep problem interventions in mental healthcare services. However, the study also has some limitations. The PSQI questionnaire is a retrospective 30-day instrument used for inclusion at the first consultation. However, we also use it for measuring short-term, i.e., 2-week, effects. This results in an interval of only 14 days between assessments at baseline and week 2. Therefore, the answers obtained in week two are biased by baseline answers and comparison may be difficult. Perhaps it would have been appropriate to delay this second data collection, but because of the short 6-week study period, the second data collection would then be placed too late in relation to the last time point.

We have no outcomes related to mental disorders, which could have strengthened the design as the relationship between, e.g., insomnia and depression has been described as bidirectional [46]. Two meta-analyses have concluded that in patients with depression and comorbid insomnia, treatment with CBT-I may lead to an improved depression outcome with a medium-to-large effect size [25, 26]. However, the present study enrolls patients with depressive disorder, bipolar disorder, and attention deficit disorder. Therefore, psychopathology outcomes for each patient group would be needed. For this, we would need larger subgroups. Another option would be to assess general psychiatric symptoms across diagnoses [10], but this would not give answers as to whether diagnostically specific symptoms were reduced. Instead, we have chosen to describe day-time functioning and general well-being with other questionnaires.

Patients in the two groups do not have comparable treatment contacts with the research team. As illustrated in Fig. 1, the intervention group had six visits during the study period and the control group had only three. This may potentially cause improvement due to non-specific treatment factors in the intervention group.

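### Structured adverse-event checks are fixed at weeks 2 and 6 with none stated at withdrawal, so non-serious events in patients who leave after week 2 are not systematically captured

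*Protocol article*

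**What the plan says.** All references are to the protocol article.

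- **Adverse event reporting and harms {22}** sets the schedule: "Patients in the intervention group will be assessed for adverse events at weeks 2 and 6". It adds: "All cases of serious adverse events will be reported to the Danish Scientific Ethics Committee". That second sentence carries no time limit.
- **Intervention description {11a}** gives "six individual sessions lasting 60 min each in the course of 6 weeks". The first item in the content list is assessment and the diary. The second is "Sleep restriction, sleep compression, stimulus-control, or phase advance".
- **Criteria for discontinuing {11b}** lets patients leave for any reason. It also lets investigators withdraw a patient who is deteriorating, for instance "if they experience a manic episode, are at an acutely increased suicide risk, or if they are hospitalized for any reason".
- **Plans for assessment and collection of outcomes {18a}** covers patients who discontinue within 7 days of the week-2 or week-6 follow-up. They may fill in the questionnaires when the actigraph is handed back, with PSQI and ISI given priority. Adverse events are not mentioned.
- **Plans to promote participant retention {18b}** offers phone, home or virtual completion of questionnaires to patients who deviate from the intervention protocol, and allows a tolerance "of 7 days from the planned follow-up visits". Again only questionnaires are named.
- **Discussion** notes that "the intervention group had six visits during the study period and the control group had only three".

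**The concern.** The behavioural components that could plausibly cause adverse effects begin at about the second session. A check at week 2 sees little of that exposure, and the next scheduled check comes at the end of the trial. A patient who stops in between has no stated adverse-event assessment on leaving, although the plan does provide a route for collecting questionnaires from some of these patients.

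The stake is selective ascertainment. If people who feel worse are more likely to stop, the events recorded by structured questioning come disproportionately from those who stayed, and the reported count is too favourable. This matters more here than in some trials. The Discussion says that no outcomes related to the mental disorders are measured, so no symptom scale would show worsening indirectly. There is no data monitoring committee. Low risk is also the stated reason for having no audit and part of the reason for having no interim analysis. A count that leans towards completers could later be read as confirming that low risk.

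**Working it through.** The plan gives no figure to reproduce here. The check is arithmetic on the schedule.

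**Inputs from the protocol article:** checks at weeks 2 and 6 ({22}); visit tolerance of 7 days either way ({18b}); six sessions in 6 weeks, with the components in question listed second ({11a}); 44 patients per group and 25% expected dropout (Sample size {14}).

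**Assumptions:** sessions are about evenly spaced; each listed content item corresponds to one session; dropout is 25% in the intervention arm; for the split over time, dropout is uniform over the 42 days.

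**1. Interval between checks**
- Nominal: day 42 − day 14 = 28 days.
- Shortest with the tolerance: day 35 − day 21 = 14 days.
- Longest with the tolerance: day 49 − day 7 = 42 days.

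**2. Active exposure seen by the nominal week-2 check**

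| Assumed spacing | Session 2 | Exposure before week-2 check | Exposure to week 6 | Share seen by first check |
|---|---|---|---|---|
| Weekly, weeks 0 to 5 | week 1 (day 7) | 14 − 7 = 7 days | 42 − 7 = 35 days | 7/35 = 20% |
| Even over weeks 0 to 6 | week 6/5 = 1.2 (day 8.4) | 14 − 8.4 = 5.6 days | 42 − 8.4 = 33.6 days | 5.6/33.6 = 17% |
| Weekly, weeks 1 to 6 | week 2 (day 14) | 14 − 14 = 0 days | 42 − 14 = 28 days | 0/28 = 0% |

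The first check therefore comes 0 to 1 week after session 2. Some 80% to 100% of the exposure up to week 6 is left to the second check.

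**3. Patients without the final check**
- Expected dropouts in the intervention arm: 0.25 × 44 = 11. This is the maximum at that dropout rate, because it treats every dropout as leaving with no final check.
- Leaving before week 2, if uniform: 11 × 14/42 = 3.7, about 4. These may miss both checks.
- Leaving between weeks 2 and 6, if uniform: 11 × 28/42 = 7.3, about 7. These were due the week-2 check but miss the final one.
- Of those 7, leaving on days 21 to 35, if uniform: 11 × 14/42 = 3.7, about 4. They fall outside both 7-day windows, so {18a} does not offer them even the questionnaires.

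**4. Which events are lost**

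Setting {22} beside {11b}: serious events are reportable whenever they occur, and an event that prompts the investigator to withdraw a patient is already known to the investigator. What neither provision covers is a non-serious event after the last check attended, or worsening in a patient who simply asks to stop.

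**The case against.** The strongest reply is that a reader could infer far more from the schedule than it supports. Three such inferences do not hold.

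- **That patients withdrawn between the checks are never assessed.** A patient leaving after week 2 was due the week-2 check, and all serious events are to be reported with no time limit. The sentence in {22} also does not say that weeks 2 and 6 are the only occasions on which an event may be noted.
- **That the events most likely to be missed are mania, suicide risk and hospitalization.** Where these lead the investigator to withdraw the patient under {11b}, they are known by definition.
- **That deterioration would go unrecognised for weeks.** Patients have six individual hour-long sessions with clinical staff, and contact with their primary nurse continues (concomitant care {11d}). The timing of a structured question is not the timing of clinical awareness.

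Other limits also stand. Session dates are inferred. Sleep restriction is one of four alternatives in the second item, so it is not every patient's starting component. Eleven of 44 is an upper figure.

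It can also be said that a condensed article leaves spontaneous reporting and withdrawal procedures to the full protocol, and that two checks in a 6-week behavioural trial are a legitimate choice. This holds only in part. If the full protocol already records adverse events at withdrawal, that part of the point falls away. But the article states a definite schedule under its harms item and describes contact at discontinuation for questionnaires alone. The point addresses that stated schedule, not an omitted detail.

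**Conclusion.** The concern holds in a limited form. Followed as written, the schedule does not systematically capture non-serious events, or worsening in patients who leave at their own request, after the last check attended. The adverse-event count therefore leans towards completers. At the planned dropout, at most about 11 of 44 intervention patients lack the final check; about 7 leave between weeks 2 and 6 under uniform dropout. If sessions are roughly weekly, that final check carries 80% to 100% of the active exposure up to week 6. The direction of the bias, towards too few events, rests on the further assumption that leaving is related to feeling worse; the documents give no data on this.

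The article does not show that serious harm would be missed or recognised late. That adverse-event assessment is stated for the intervention group only is a separate matter. It means the plan contains no between-arm comparison of harms that this schedule could distort. The change is worth making because it is cheap and removes an avoidable selection, not because the trial is unsafe as designed.

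**What to change.** Amend Adverse event reporting and harms {22} so that, besides weeks 2 and 6:

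1. a short, identical adverse-event form is completed at each of the six existing sessions;
2. the same form is completed at any withdrawal, whenever it occurs, at actigraph return or by phone;
3. events are reported for all intervention patients, including those who withdrew, with the number assessed at each time point.

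If adverse events are ever also collected in the control group, compare the arms only on the assessments common to both, so that the extra contacts in the intervention arm do not inflate its count.

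The cost is one additional REDCap form, a few minutes per session and an occasional phone call. Session-level counts would have no control-arm counterpart and could only be described. Treatment and visit schedule are unchanged.

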**Methods:**

The study is a randomized controlled trial enrolling 88 outpatients with bipolar disorder, major depression, or attention deficit disorder with symptoms of various sleep problems (insomnia, circadian rhythm disorders, or hypersomnia). Patients are allocated to either an intervention group receiving six sessions of transdiagnostic sleep treatment or to a control group receiving a single session of sleep hygiene education. Assessments are made at baseline, at week two, and after 6 weeks in both groups. Actigraphy is performed continuously throughout the 6-week study period for all patients. The primary outcome is changes in the subjective appraisal of sleep quality (Pittsburgh Sleep Quality Index). The secondary outcomes are changes in sleep efficiency, sleep onset latency, wake after sleep onset, number of nocturnal awakenings (based on actigraph and sleep diary data), changes in insomnia severity (Insomnia Severity Index), well-being (WHO-5 Well-Being Index), personal recovery (INSPIRE-O), work ability (Work Ability Index), and consumption of sleep medication (sleep-diaries).

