### Trial design {8}

The study is a randomized controlled trial enrolling 88 outpatients with sleep problems (symptoms of chronic insomnia, circadian rhythm disorders, or hypersomnia) comorbid to BD, UD or ADHD. Patients are allocated to two parallel groups; an intervention group receiving six sessions of transdiagnostic sleep treatment or a control group receiving one session of sleep hygiene education. The allocation ratio is 1:1. After 6 weeks, the control group is offered the sleep intervention, but the data collected from this group will not be included in the present project.

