### Sample size {14}

A power calculation was performed based on the results of a similar study [28] with PSQI as a secondary outcome using an average effect size of 0.67. Assuming a power of 0.80, a significance level of 0.05, and an expected power magnitude of 0.67, a sample size of *n* = 44 is obtained for each group. The expected 25% dropout rate is based on former experiences from a pilot project (*n* = 55). A total of 88 patients will be included in the study.

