
All patients complete the six validated questionnaires at personal visits at baseline (week 0) and again after 2 and 6 weeks. Patients are asked to wear actigraphs around the clock during all 6 weeks and to complete a short sleep diary on a daily basis (see Additional files 2 and 3). Furthermore, they complete the morningness-eveningness questionnaire (MEQ) at week 2 to estimate their chronotype. This validated questionnaire has scores ranging from 16 to 86. Scores of 41 and below indicate “evening types.” Scores of 59 and above indicate “morning types.” Scores between 42 and 58 indicate “intermediate types” [43]. For the study schedule used for enrolment, intervention, and assessments, please see Table 1.

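### Adverse events are actively assessed in the intervention group only, although both groups attend in person at weeks 2 and 6, so the trial cannot compare adverse events between arms without bias

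*Protocol article*

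**What the plan says.** The section on adverse event reporting and harms {22} has two sentences. The first sets the assessment: "Patients in the intervention group will be assessed for adverse events at weeks 2 and 6". The second covers serious events and names no arm: "All cases of serious adverse events will be reported to the Danish Scientific Ethics Committee".

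Other sections describe the contacts available in each arm:

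- Abstract, Methods: "Assessments are made at baseline, at week two, and after 6 weeks in both groups".
- Data management {19}: "All patients complete the six validated questionnaires at personal visits at baseline (week 0) and again after 2 and 6 weeks".
- Discussion: "As illustrated in Fig. 1, the intervention group had six visits during the study period and the control group had only three".

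The section on discontinuing or modifying interventions {11b} states: "The investigators have the discretion to withdraw patients from the study if their mental disorder is deteriorating". It gives a manic episode, acutely increased suicide risk and hospitalisation as examples, and does not restrict the rule to one arm. The blinding section {17a} says that allocation cannot be blinded.

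No reason is given for leaving controls out of the adverse event assessment.

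**The concern.** The harms sentence is a stated rule. It names the arm and the weeks, so it is not a detail left to a fuller document. Followed as written, it produces systematic adverse event data in one arm of a randomised trial.

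That matters in this population. Participants have bipolar disorder, unipolar depression or attention deficit disorder, and the events named in section {11b} can arise from the underlying illness. If some occur in the intervention group, the natural question is whether they exceed what would have happened anyway. The control group exists to answer that, but it is not asked.

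The error can go either way. Background illness may be counted against the intervention, or a real excess may be dismissed as background. The Discussion also says that the trial has no outcomes related to the mental disorders themselves, so no symptom scale would show psychiatric worsening by arm.

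**Working it through.** The protocol gives no adverse event rate, so there is no figure to reproduce. The check has two parts.

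**1. What each arm provides under the plan**

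| Source of harms information | Intervention | Control |
|---|---|---|
| Active questioning at weeks 2 and 6 ({22}) | Yes | Not planned |
| In-person visit at weeks 2 and 6 ({19}, Abstract) | Yes | Yes |
| Number of visits (Discussion) | 6 | 3 |
| Serious adverse event reporting ({22}) | Yes | Arm not restricted |
| Withdrawal for deterioration ({11b}) | Yes | Arm not restricted |

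The three control visits fit baseline, week 2 and week 6, so logistics do not explain the omission. For non-serious events the control column is empty. For serious events both columns have an entry, but the chance of detection differs: one arm has twice the visits (6/3 = 2) and is questioned directly, and staff and patients know the allocation.

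**2. What a one-arm count can and cannot show (illustration)**

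Inputs from the protocol: "A total of 88 patients will be included in the study" (Sample size {14}) and "The allocation ratio is 1:1" (Trial design {8}), so 88/2 = 44 per arm. The event counts below are assumptions.

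Suppose 9 of 44 intervention patients report an event: 9/44 = 20.5%, exact 95% confidence interval 9.8% to 35.3%. Under the plan as written, that is all that can be reported for actively assessed events. With control counts, the risk difference is 9/44 - x/44. Its Newcombe 95% interval, where l and u are the Wilson limits for each proportion (1 = intervention, 2 = control), is

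lower = d - sqrt[(p1 - l1)² + (u2 - p2)²], upper = d + sqrt[(u1 - p1)² + (p2 - l2)²].

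| Assumed control events | Risk difference (points) | 95% interval |
|---|---|---|
| 0/44 | +20.5 | 8.2 to 34.5 |
| 4/44 | +11.4 | -3.9 to 26.4 |
| 9/44 | 0.0 | -16.8 to 16.8 |
| 13/44 | -9.1 | -26.5 to 9.0 |

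Worked row for 9/44 against 9/44: p = 0.2045 and the Wilson limits are 0.1115 and 0.3450. The half-width is sqrt[(0.2045 - 0.1115)² + (0.3450 - 0.2045)²] = sqrt(0.00865 + 0.01974) = 0.168.

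The same intervention count fits a clear excess, no difference, or fewer events than in controls. One-arm data cannot separate these.

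The intervals also show the limit of the remedy. Even with both arms assessed, the difference is uncertain by roughly 13 to 18 points either way. With the 25% dropout expected in {14} (44 × 0.75 = 33 per arm), equal counts of 7/33 give ±19.6 points.

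**The case against.** The strongest objection concerns scope. A reader might infer that the control arm yields no harms information at all. The documents do not support that. Serious events are to be reported whatever the arm, and the withdrawal criteria cover the very events of most concern in both arms. Sleep quality, insomnia severity and well-being are measured in both arms at all three time points, and sedative and hypnotic use is recorded daily. What is one-sided is active questioning about adverse events. This objection stands and sets the limits of the point. It does not remove it, because passive reporting in an open-label trial with unequal contact is not equal ascertainment.

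A reader might also infer that the efficacy result is compromised. It is not. The Objectives {7} contain no safety hypothesis, and the primary outcome, the Pittsburgh Sleep Quality Index, is collected in both arms on the same schedule.

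Nor does it follow that the low-risk premise is wholly untestable. Absolute event rates in treated patients are still observed. The protocol also rests the absence of interim analysis partly on the short trial duration, and the Discussion says that the treatment has been standard care in the department for some years. What is lost is attribution.

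The gain in precision is modest, as the intervals above show: a descriptive estimate, not a decisive test. That is also fair.

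Finally, Table 1 and Fig. 1 are not visible in the text reviewed, and either might list an adverse event check for controls. If so, the documents would conflict and the harms sentence would still need correcting.

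**Conclusion.** The point holds in a limited form. Active adverse event assessment is planned for one arm only, although the other arm attends at the same weeks. Non-serious events would have no planned control data, and serious events would be detected unequally. No unbiased between-arm comparison of adverse events is possible under the plan as written.

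The defect has no single numerical size, because the protocol gives no event rates. With assumed counts, one intervention-arm result is compatible with differences from +20.5 to -9.1 points. This rests on 44 patients per arm, on reading the harms sentence as written, and on no contrary entry in the table and figure not shown.

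It limits the safety conclusion only. It is a worthwhile, inexpensive improvement and falls short of a change that the trial's main result depends on.

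**What to change.** Amend the first sentence of the harms section so that both groups are asked about adverse events, with identical questions, at the week-2 and week-6 visits. Report counts by arm and risk differences with 95% confidence intervals, including manic episodes, suicidality, hospitalisation and withdrawal for deterioration. State that at about 44 per arm these estimates are imprecise and descriptive.

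Recruitment began in May 2022, so some controls may already have finished without being asked. Any review of health records for completed patients should use the same items and time window in both arms. It should be reported separately as a partial recovery and not pooled with the prospective answers. Data management {19} lists only identifiers, diagnosis and medication prescriptions from hospital records, so such a review would add data items.

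The cost is a few minutes per control visit, with no added visits and no change to the total of 88. Because study procedures change, the section on protocol amendments {25} calls for a formal amendment and ethics approval.
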